### Concealment mechanism {16b}

The allocation sequence was created during the course of an online video call with representatives of all study centers. The resulting allocation was immediately communicated to the centers; no concealment was used.

### Implementation {16c}

The allocation sequence and accordingly the assignment of the centers to study arms was generated by the study's statistician, who is employed at one of the study centers. Participants (employees and patients) are enrolled by representatives of the centers at their respective locations.

## Assignment of interventions: blinding

### Who will be blinded {17a}

Due to the open nature of the intervention, the staff of the study centers is not blinded to the intervention. Patient-centered data is collected retrospectively and anonymously as part of routine documentation of patient care. According to German legislation, this retrospective use is possible without informed consent; as such, patients will not be informed about the study and thus no blinding is applied.

### Procedure for unblinding if needed {17b}

Not applicable as explained in the previous section.

## Data collection and management

### Plans for assessment and collection of outcomes {18a}

Data collection of the primary and secondary outcome parameters will take place during three time periods (T0, T1, T2). Primary staff-centered and patient-centered outcomes will be obtained via digital records of the participating study center at each site.

#### T0 (baseline)

Data collection period T0 will start 3 months (90 days) before the start of the study and will last for 45 days. Due to administrative aspects at the local study centers, the specific starting point for T0 might vary between study centers, such that within a total time frame of 61 days all data will be collected for 45 consecutive days at each site. Patient-centered data will be collected during the first 45 days with the start of T0. Sickness-related absence (staff-centered primary outcome) will be obtained during the first 30 days with the start of T0. Questionnaire data will be collected during the last 30 days of T0.

#### T1

Data collection period T1 will start 1 month after the start of the study and will last for 45 days. Equivalent to T0, patient-centered data will be collected during the first 45 days of T1, and sickness-related absence will be obtained during the first 30 days. Questionnaire data will be collected during the last 14 days of T1.

#### T2

Data collection period T2 will start 4 months after the start of the study and will last 45 days. All outcome parameters will be obtained as in data collection period T1.

### Plans to promote participant retention and complete follow-up {18b}

To promote participation in the online survey, 20 gift vouchers in the amount of 20€ each per data collection period will be raffled among participating employees. All other data does not rely on study participation of employees or patients; thus, no other measures are planned to promote participant retention.

### Data management {19}

Patient-centered study data will be saved on secured institute drives at each site. The section of the respective drive is only accessible to the persons involved in the study and is protected from unauthorized access by appropriate software as part of the IT support of the respective site. Data will be deleted from the servers after study completion when binding storage regulations have expired. Study staff and the PI(s) at each site will be responsible for evaluating the accuracy, consistency, and completeness of the data obtained at their site before disseminating their data to the lead project partner University Hospital RWTH Aachen, AIXTRA Competency Center for Training and Patient Safety. The complete study data will be stored in a high-security computer database at the location of the lead project partner, ensuring confidentiality in accordance with national data legislation and Good Clinical Practice (GCP). All persons and third parties involved in performing the study analyses (e.g., statisticians) are bound to secrecy and guarantee that no personal data will be coded in the course of the analysis or passed on to third parties or persons not involved in the study.

### Confidentiality {27}

Data collection (both patient- and staff-centered) will be anonymous. Personal data of ICU staff will not be collected and will not be subject to any statistical analyses. Staff councils at each study site were informed about the study and provided their consent. All patient data that serve as the basis for the primary and secondary outcome parameters are collected on a regular basis as part of the documentation of patient care. The data will be collected and stored pseudonymously. The number and severity of intensive care complications will be coded on the basis of the available data by trained study staff.

### Plans for collection, laboratory evaluation, and storage of biological specimens for genetic or molecular analysis in this trial/future use {33}

Not applicable, since no such samples are collected in this study.

## Statistical methods

### Statistical methods for primary and secondary outcomes {20a}

Data will be analyzed with IBM SPSS Statistics software version 25 (IBM Corp., Armonk, NY, USA). To analyze the effect of the ICU Support intervention on the patient-centered primary outcome, an analysis of covariance with time as the within-subject factor (T0 and T1), study group as the between-subject factor (intervention and control), and 4 covariates (age, sex, previous illnesses, and length of stay) will be conducted. Significance will be determined by two-sided 95% confidence intervals.

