### Who will take informed consent? {26a}

Patient-centered outcomes will be anonymously obtained at the unit level at each study site via digital patient records as part of the routine documentation of patient care. Since patients will not receive any study-related intervention directly, they will not be included as study participants but define the patient population through which the quality of care is assessed at each site. Staff-centered outcomes will also be anonymously obtained at the unit level via the Human Resources (HR) department of each clinic and via an online questionnaire using the software SoSci Survey. This software meets the national and international legal requirements for data protection (BDSG, DSG-VO and state laws, ISO-certified). Prior to the participation in the questionnaire, ICU staff will be informed about the study that their participation is voluntary and that non-participation will not result in any negative consequences. Moreover, they will be informed that they can withdraw their participation at any time without providing any reason. Participants can only access the questionnaire after providing online informed consent to participate in the online surveys.

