#### ICU patients

An analysis of covariance (ANCOVA; fixed effects, main effects, and interactions) with two groups, two measurement times (T0 and T1), and 4 covariates (age, sex, previous illnesses, and length of stay) was scheduled to calculate the appropriate sample size. Assuming a small effect of *f* = 0.10 according to Cohen (1988) [16], an alpha error level of 0.05 and a power of 90%, the total sample size was *N* = 1053. To account for an expected dropout of 10%, a total number of 1110 patients will be targeted.

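### The primary patient model treats time (T0, T1) as within-subject, but the two windows contain essentially different patients, and the sample size was computed for a between-patient model

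*Protocol article*

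**What the plan says.** All references are to the protocol article.

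- **Analysis.** Section {20a} gives the model for the patient-centered primary outcome as "an analysis of covariance with time as the within-subject factor (T0 and T1" being its levels, with "study group as the between-subject factor (intervention and control" as the arms and "4 covariates (age, sex, previous illnesses, and length of stay) will be conducted". On inference it says only: "Significance will be determined by two-sided 95% confidence intervals". It does not say which term is the treatment effect.
- **Outcome.** Section {12} defines one complication count per patient for the ICU stay.
- **Windows.** Under {18a}: "Data collection period T0 will start 3 months (90 days) before the start of the study and will last for 45 days". Sites may shift their start, provided the 45 consecutive days fall within a 61-day frame. For the next period: "Data collection period T1 will start 1 month after the start of the study and will last for 45 days".
- **Patients.** Section {10} admits adults with an ICU stay of 24 h or more and does not require presence in both periods. Section {26a} says patients are not study participants but serve to describe care at each site, and that "Patient-centered outcomes will be anonymously obtained at the unit level at each study site via digital patient records". Section {27} calls data collection anonymous but also says the patient data are held pseudonymously.
- **Sample size.** Section {14}, ICU patients, uses "An analysis of covariance (ANCOVA; fixed effects, main effects, and interactions) with two groups, two measurement times (T0 and T1" as the levels, four covariates, f = 0.10, alpha 0.05 and 90% power, and arrives at N = 1053.

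**The concern.** The covariates are patient characteristics and the outcome is counted per patient, so the subject in {20a} is the patient. A within-subject factor requires the same patient to be measured at both levels, and its error term is built from the within-patient T0-to-T1 differences. Nothing in the design provides those pairs: the windows are far apart, stays can be as short as a day, and nobody is followed from one window to the next.

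A repeated-measures procedure run as worded would use only patients with both values, so it would discard nearly all the data collected. An analyst who departs from the wording has to choose a model after the fact, with no named treatment term to hold to. Either way, the model for one of the two primary hypotheses is not properly fixed in advance.

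**Working it through.** **1. Gap between the windows** (day 0 = study start; one month taken as 30 days)

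- T0 ends at -90 + 45 = day -45. T1 starts at about day +30. Gap = 30 - (-45) = 75 days.
- If the 61-day frame opens at day -90 and a site uses its last 45 days, T0 ends at -90 + 61 = day -29. Gap = 30 - (-29) = 59 days.

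To contribute to both periods a patient would need an ICU stay longer than 59 to 75 days, or a readmission to the unit. The article gives no length-of-stay distribution or readmission rate, so the number of such patients cannot be computed. Few if any is an inference from the windows and the eligibility rule.

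**2. The plan's own sample size**

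Inputs from {14}: f = 0.10, alpha = 0.05, power 90%, 2 groups, 2 times, 4 covariates. For a fixed-effects ANCOVA with each patient counted once:

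- noncentrality λ = f² × N
- numerator df = 1
- denominator df = N - cells - 4

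The smallest N reaching 90% power is **1053**, with 4 cells (2 arms × 2 periods) and also with 2. At N = 1053, λ = 0.01 × 1053 = 10.53, the denominator df with 4 cells is 1053 - 4 - 4 = 1045, and power is 90.0%. As a cross-check, the normal approximation for two means differing by 0.2 SD gives 1052 in total. The stated figure is therefore reproduced as a between-patient calculation. In the four-cell reading it is the total over both arms and both periods.

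**3. The model worded in {20a}**

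For a within-between interaction with m = 2 measurements per patient, λ = f² × N × m / (1 - ρ), where ρ is the within-patient correlation. The article states no ρ, so a range is assumed:

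| Assumed ρ | Patients needed, each measured twice | λ |
|---|---|---|
| 0 | 528 | 0.01 × 528 × 2 / 1 = 10.56 |
| 0.3 | 370 | 0.01 × 370 × 2 / 0.7 = 10.57 |
| 0.5 | 265 | 0.01 × 265 × 2 / 0.5 = 10.60 |
| 0.7 | 160 | 0.01 × 160 × 2 / 0.3 = 10.67 |

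The requirement falls as ρ rises, so no non-negative correlation gives more than 528. Sections {14} and {20a} describe different models, and only the one in {14} suits records that count each patient once.

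**4. What f = 0.10 means for the corrected term**

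In a balanced 2 × 2 layout the difference in differences has standard error 4σ/√N. Setting (Δ/SE)² = Δ²N/(16σ²) equal to f²N gives Δ = 4fσ = 0.4σ. A plain comparison of two arms at f = 0.10 detects 2fσ = 0.2σ. The N of 1053 therefore carries over to the interaction at the stated f, and f then refers to the interaction.

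**The case against.** **The label is a slip, and the right model is already in the article.** Section {14} sizes a between-patient ANCOVA with interactions, and an analyst would probably enter period that way. This has force: it makes the remedy small, and it means a reader should not conclude that the primary hypothesis is bound to go untested. But {20a} is the section that governs the analysis, and it states the other model. This is a stated rule that conflicts with the design, not detail left to an analysis plan.

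**The subject could be the centre.** Data are obtained at unit level, and each centre is observed in both periods, so the model could be fitted to centre means. A claim that the model cannot be fitted at all would therefore go too far. The reading still sits badly with four patient-level covariates and N = 1053, since it leaves nine subjects. What the documents support is a mismatch with patient-level data.

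**The records might be linkable.** A reader might infer from {26a} that T0 and T1 records can never be linked. Section {27} also describes the data as pseudonymous, which would in principle allow linkage, so the article conflicts with itself here and does not establish that linkage is impossible. The point does not depend on it: full linkage would pair only very long-stay or readmitted patients.

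**Conclusion.** The specification in {20a} is wrong as written for patient-level data and inconsistent with {14}. T0 and T1 are repeated cross-sections about 75 days apart (59 at the least), so a within-patient time factor has few if any pairs to work with. The stated N = 1053 matches a between-patient ANCOVA exactly and is about twice the largest within-subject figure (1053 / 528 ≈ 2.0).

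This rests on three assumptions:

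- the subject is the patient, as the covariates and outcome definition imply;
- very long stays and readmissions are rare, which the article does not quantify;
- the within-patient correlation is not negative.

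A count of exactly zero paired patients should not be claimed. The wording needs correcting before analysis, but the correction does not itself invalidate the planned pre-dropout sample size.

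**What to change.** In {20a}, delete the within-subject description of time. State that period (T0, T1) is a between-patient factor alongside arm, and name the arm-by-period interaction as the treatment effect whose two-sided 95% confidence interval decides the hypothesis. In {14}, say that f = 0.10 refers to that interaction. Reconcile the anonymous and pseudonymous statements in {26a} and {27}.

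The cost is a few sentences and the matching analysis code. No extra data are needed, and N before dropout stays at 1053 at the stated f.

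Two limits apply:

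- Comparing T1 outcomes with the centre's T0 mean as a covariate is an alternative, not an equivalent. The interaction fixes the baseline adjustment at a slope of 1, while the covariate model estimates the slope, and with nine centres the two can give different answers. One must be chosen in advance.
- Centre is the only unit measured repeatedly. Adding centre and centre-by-period effects belongs to the separate matter of clustering. Its price is that inference then rests on nine centres, and the 90% power in {14} would have to be restated.

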### Outcomes {12}

#### Patient-centered primary outcome

Number of intensive care complications per patient during the stay in the intensive care unit during T1. The definition of complications is a priori based on the classification scheme according to Clavien and Dindo [13]. This includes a 5-level graduation of complications by severity. The primary outcome only considers the number of complications, not their severity. Data collection of patient-centered outcomes will be retrospectively obtained from patient records at each participating study center and will be coded by trained study staff.

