## Assignment of interventions: allocation

### Sequence generation {16a}

The nine participating study centers were randomly assigned to the intervention or control arm prior to the start of the study, using a web-based randomizer [18]. Following this procedure, four study centers were assigned to the intervention arm and five study centers were assigned to the control arm.

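### Nine hospitals are randomised, but the patient-level primary model and the 90% power both treat patients as independent, so the 95% interval is too narrow unless centre effects are almost perfectly stable

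*Protocol article*

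**What the plan says.** All references are to the Protocol article.

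- **Randomised unit.** Sequence generation {16a}: "The nine participating study centers were randomly assigned to the intervention or control arm prior to the start of the study". The result was that "four study centers were assigned to the intervention arm and five study centers were assigned to the control arm". Under Trial design {8} and Intervention description {11a}, the intervention is introduced for whole ICU teams.
- **Outcome.** The patient-centred primary outcome in {12} is "Number of intensive care complications per patient during the stay in the intensive care unit during T1", so it is measured on individual patients.
- **Analysis.** Section {20a} names an analysis of covariance with time (T0, T1) as the within-subject factor and "study group as the between-subject factor (intervention and control), and 4 covariates (age, sex, previous illnesses, and length of stay) will be conducted". It adds: "Significance will be determined by two-sided 95% confidence intervals". Section {20b} intends no further analyses.
- **Sample size.** Section {14}, ICU patients, uses the same patient-level layout. It starts from "Assuming a small effect of *f* = 0.10" and reports "an alpha error level of 0.05 and a power of 90%, the total sample size was *N* = 1053". No ICC, design effect, random effect, robust variance or centre-level summary appears in either section.

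**The concern.** Allocation varies only between hospitals, so the evidence on the intervention comes from four centres against five. A model with group, time and patient covariates takes its error term from over a thousand patients. Anything that moves one hospital's complication count between T0 and T1 relative to the others, such as staffing, a local infection wave or a change in documentation, is then credited to or held against the intervention with far too much certainty.

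At stake is the decision rule for one of the two primary hypotheses: the interval may not cover at 95%, and the power that justified the design was calculated for a different design. This is not detail left to a separate analysis plan. The article fixes the model's factors, covariates and decision rule, and gives a numerical power claim with its inputs.

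**Working it through.** **1. Reproduce the plan's figure.** Inputs from {14}: f = 0.10, alpha 0.05, power 90%, 4 covariates, 2 groups. Fixed-effects ANCOVA: noncentrality = N × f², numerator df = 1, denominator df = N − groups − 4. At N = 1053 the noncentrality is 10.53 and power is 0.9001, with either 2 groups or 4 group-by-time cells; at 1052 it is 0.8998. So 1053 reproduces exactly, with a denominator of about 1047 degrees of freedom and independent patients.

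**2. What f = 0.10 can mean.** {14} does not say which term it refers to, and N is the same either way.
- Group main effect: arm means at ±0.10 SD, a difference of 0.20 SD.
- Group-by-time interaction: four cells at ±0.10 SD, a difference-in-differences of 4 × 0.10 = 0.40 SD.

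**3. Group-by-time contrast.** Assumptions: 1053 patients over both periods, equal centres, so m = 1053 / (9 × 2) = 58.5 per centre-period; ICC 0.01 to 0.10; cluster autocorrelation (CAC, the correlation of a centre's effect between T0 and T1) 0.5 to 1. Neither ICC nor CAC is in the documents.

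- Variance inflation: VIF = ICC(1 − CAC)m + (1 − ICC)
- False-positive rate of the stated analysis: 2[1 − Φ(1.96/√VIF)]
- Standard error of the centre-level contrast: √{2[ICC(1 − CAC) + (1 − ICC)/m](1/4 + 1/5)}
- Power: noncentral t on 4 + 5 − 2 = 7 df, noncentrality 0.40/SE

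Example, ICC 0.05 and CAC 0.8: VIF = 0.05 × 0.2 × 58.5 + 0.95 = 1.535, false-positive rate 11%. SE = √(2 × 0.02624 × 0.45) = 0.154, noncentrality 2.60, power 61%.

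| CAC | False-positive rate at ICC 0.01 / 0.02 / 0.05 / 0.10 | Power, 7 df |
|---|---|---|
| 0.5 | 8 / 12 / 21 / 32% | 69 / 60 / 43 / 30% |
| 0.8 | 6 / 7 / 11 / 17% | 75 / 71 / 61 / 49% |
| 0.9 | 6 / 6 / 8 / 11% | 77 / 75 / 70 / 62% |
| 1.0 | 5 / 5 / 4 / 4% | 79 / 80 / 81 / 83% |

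VIF exceeds 1 whenever (1 − CAC)m > 1, that is, CAC below 1 − 1/58.5 = 0.983. At ICC 0, power on 7 df is 79%.

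**4. Between-arm contrast at T1.** Taking d = 0.20 and all 1053 patients in T1, m = 1053/9 = 117. At ICC 0.01 the design effect is 1 + 116 × 0.01 = 2.16. The correct interval is √2.16 = 1.47 times the stated one, the false-positive rate is about 18%, and power on 7 df is 47% (SE = √(2.16/117 × 0.45) = 0.091, noncentrality 2.19).

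**5. If 1053 were per period.** With m = 117 per centre-period and 0.40 SD, power at ICC 0.01 / 0.02 is 87 / 76% at CAC 0.5, 94 / about 90% at 0.8 and 96 / 94% at 0.9. At ICC 0.05 and 0.10 with CAC 0.5 it is 51% and 33%.

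**The case against.** The strongest reply is that T0 is in the model. In a group-by-time contrast the stable part of any centre difference (usual case mix, coding habits) cancels. This stands as far as it goes: the last row of the table shows no inflation when centres are perfectly stable. But T0 starts 90 days before study start and T1 one month after it ({18a}), and nothing in the documents supports near-perfect stability over that gap. Treating time as within-subject does not supply the missing term either: patients in separate 45-day windows are largely different people, and what recurs is the centre.

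A reader might infer that 90% power is out of reach under any reading. The documents do not support that. If 1053 were a per-period number, 90% is attainable at low ICC with high autocorrelation, or with perfectly stable centres. Section {14} calls 1053 a total, however, and {15} says only that the periods were made long enough for sufficient patients.

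A reader might also take f = 0.10 to mean a 0.40 SD difference between arms at T1. The plan does not identify the term, and 0.40 SD is a difference-in-differences, not a T1 difference. Nor does the range of 51 to 212 employees in {9} establish unequal patient numbers. Unequal centres would lower power, but the article gives no patient counts per centre.

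Finally, {14} records planning already done, and Trial status says the intervention is running in both arms. That limits what a new power figure can change. It does not affect the analysis, which can still be corrected.

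**Conclusion.** The point holds. The stated primary analysis ignores the randomised unit, and the 90% is a power for independent patients. The interval is too narrow unless the tested term is group by time and centre effects are essentially unchanged between T0 and T1. With 1053 as a total, power on 7 df is at most about 79–83% even with perfectly stable centres, so 90% is not delivered as stated.

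How far the error rate and power depart from 5% and 90% is not known. It depends on an ICC and an autocorrelation that the documents do not give, on equal centre sizes, and on which term carries f = 0.10. The figures above are therefore ranges under stated assumptions. The issue must be resolved before analysis because it governs the inference on a primary outcome.

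**What to change.** - **Design wording:** describe the trial as cluster-randomised, with the centre as the unit.
- **Section {20a}:** before analysis, choose one approach that respects the centre and take the 95% interval from it. One option is a mixed model with random centre and centre-by-period effects and small-sample degrees of freedom. The other is a centre-level comparison: T1 adjusted for the centre's T0 mean (6 df), or centre changes (7 df). The two weight patients differently if centres are unequal, so they are alternatives, not interchangeable. State which term is the test of the intervention. The choice of covariates is a separate matter, and this change does not depend on it.
- **Section {14}:** keep 1053 as the planning record, but state that its 90% assumes independent patients and say which term f = 0.10 refers to. Add the power or detectable effect of the chosen analysis for four against five centres, over a stated range of ICC and autocorrelation.

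The cost is wording and reanalysis. Centre membership is known and T0 is collected at every site, so no new data are needed. The price is wider intervals and a less favourable stated power.

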**Methods:**

ICU Support will be implemented at nine university hospitals located in Germany, following a two-arm randomized parallel group design with an intervention and a control condition and three data collection periods. In the intervention arm, leading ICU personnel (physicians and nurses) will be trained in ICU Support and implement the ICU Support elements into the daily work routine of their units upon completion of data collection period T0 (baseline). In the control arm, ICU Support will not be implemented until the completion of the data collection period T1 (1 month after study start). Until then, the regular daily schedule of the ICU teams will be maintained. The final data collection period (T2) will take place 4 months after the start of the study. Primary outcomes include the number of intensive care complications per patient during their ICU stay during T1 and the sick-related absence of ICU staff during T1. Secondary outcomes include, among others, the average severity of intensive care complications per patient and employee self-reported data regarding their teamwork and patient safety behaviors.

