### Objectives {7}

The aim of the research project presented here is to evaluate the effectiveness of ICU Support regarding (1) ICU patient outcomes and (2) ICU staff outcomes. More concretely, the *primary objective* of this study is to test the hypotheses that the ICU Support intervention (a) reduces the occurrence of complications in intensive care patients and (b) reduces sickness-related absence among intensive care unit staff. *Secondary study objectives* include investigating whether ICU Support improves the perception of ICU staff regarding team collaboration and interaction related to patient safety, as well as exploring how potential effects of the ICU Support intervention develop over time.

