### Sample size {14}

Sample size calculations were performed with the statistical software G*Power software version 3.1.9.7 [15] and were based on the respective primary outcome parameter.

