#### ICU staff

The sample size calculation for the staff-centered outcomes was based on the relative risks (RR) of the two groups (intervention/control) for the measurement times T0 and T1. A small effect of RR = 1.22 according to Olivier et al. (2017) was assumed [17], an average work loss of 2.5% before the intervention, an alpha error level of 0.05, and a power of 90%. This resulted in a total sample of *N* = 37,484 h per time point. Assuming a dropout of 10%, a total number of *N* = 293 employees will be targeted.

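### Two primary hypotheses are each planned at 5% with no multiplicity or joint-success rule; if either alone can support a claim, two-sided familywise error is up to 10% (false benefit up to 5% instead of 2.5%)

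*Protocol article*

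**What the plan says.** Objectives {7} states one primary objective with two directional hypotheses, that the intervention "reduces the occurrence of complications in intensive care patients and (b) reduces sickness-related absence among intensive care unit staff". The Methods part of the abstract names two primary outcomes, "the number of intensive care complications per patient during their ICU stay during T1 and the sick-related absence of ICU staff during T1".

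Sample size {14} says that the calculations "were based on the respective primary outcome parameter". The patient part uses "an alpha error level of 0.05 and a power of 90" per cent and arrives at 1053 patients. The staff part uses "an alpha error level of 0.05, and a power of 90" per cent and arrives at 37,484 hours per time point.

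Section {20a}, whose heading covers primary and secondary outcomes, describes an analysis of covariance for the patient outcome and then says: "Significance will be determined by two-sided 95% confidence intervals". It describes no model for the staff outcome. The article gives no alpha split, no testing order and no statement that both primary outcomes must be significant.

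**The concern.** Both hypotheses concern the same intervention, in the same nine randomised centres, under a single primary objective. With no rule joining them, a significant result on either outcome could be reported as success on a primary outcome. Two chances at 5% each give an overall error above 5%.

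At stake is the error rate behind the trial's main conclusion, and whether the stated 90% power would survive a rule that brings that error back to 5%.

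**Working it through.** **Inputs.** Patient outcome ({14}): Cohen's f = 0.10, four covariates, two groups by two times, alpha 0.05, power 90%, N = 1053. Staff outcome ({14}): 2.5% of hours lost, relative risk 1.22, alpha 0.05, power 90%, N = 37,484 h. Criterion ({20a}): two-sided 95% intervals. One numerator degree of freedom is inferred from the two-by-two layout.

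**Step 1: do the stated sizes rest on an unadjusted 5%?**

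- Patients: noncentral F with noncentrality f² × N = 0.01 × 1053 = 10.53, 1 numerator degree of freedom, and N minus 4 cells minus 4 covariates = 1045 denominator degrees of freedom. At alpha 0.05 the power is 0.9001, and 1053 is the smallest N that reaches 90%. At alpha 0.025 the smallest N would be 1244.
- Staff: two proportions, 0.025 and 0.025 × 1.22 = 0.0305, with pooled variance under the null and no continuity correction: n per arm = [z(1−α/2) √(2p̄(1−p̄)) + z(0.90) √(p₁(1−p₁) + p₂(1−p₂))]² / (p₁ − p₂)². With p̄ = 0.02775 and two-sided alpha 0.05, this is (1.960 × 0.23229 + 1.2816 × 0.23226)² / 0.0055² ≈ 18,742 after rounding up. The total is 2 × 18,742 = 37,484, the stated figure. At two-sided 0.025 it would be 44,274.
- One nearby variant: a reduction from 2.5% to 2.05% tested one-sided at 5% gives 37,462, close but not equal. It also conflicts with the two-sided criterion in {20a}.

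Both stated sizes are therefore reproduced exactly at an unadjusted two-sided 5%.

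**Step 2: error over the two tests when neither effect exists.** This assumes that either result may support a claim and that each test holds its nominal 5%.

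- Any significant primary result, independent tests: 1 − 0.95² = 0.0975. Upper bound for any dependence: 0.05 + 0.05 = 0.10.
- With correlated normal test statistics: 9.5% at r = 0.3, 9.1% at r = 0.5, 7.8% at r = 0.8.
- False claims of benefit only: each two-sided 5% test contributes 2.5%, so 1 − 0.975² = 0.0494 if independent, and at most 0.025 + 0.025 = 0.05. A single test gives 0.025.

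**Step 3: power under Holm at the stated sizes.**

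- First step (alpha 0.025): 0.841 for patients (N = 1053) and 0.841 for staff (37,484 h).
- Under Holm an outcome also succeeds if its p-value lies between 0.025 and 0.05 and the other is at or below 0.025. If both planned effects hold and the tests are independent, power for each outcome is 0.841 + (0.900 − 0.841) × 0.841 = 0.891.

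**Step 4: the alternative rule.** If both outcomes must be significant at 5%, a false claim of joint success has probability of at most 5%, and no adjustment is needed. Under independence, power for joint success is 0.90 × 0.90 = 0.81.

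**The case against.** The strongest reply is that these are two separate questions: different populations, different data sources (patient records and personnel departments) and separate sample sizes. If each is reported strictly as its own claim, each carries its own 5%, and whether to adjust across distinct hypotheses is a debated choice. This has weight, because the article states no either-or success rule. But it joins the hypotheses under one primary objective for one intervention, and nothing prevents either result from being presented as success on a primary outcome.

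A second reply is that a multiplicity rule commonly sits in the statistical analysis plan, which is not shown. Silence alone would indeed be no finding. The point rests on what is printed: alpha 0.05 for each outcome, sizes that match that level exactly, and 95% intervals as the criterion. A split of alpha elsewhere would contradict these. A fixed testing order or a both-must-succeed rule would be compatible with sizing each at 0.05, but the article states neither.

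Third, the interval sentence follows the patient model, and no staff test is described. That stands. The level of the staff test is an inference from the section heading, the planning alpha and the reproduced 37,484 h.

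A reader might infer that there is a 10% chance of wrongly declaring ICU Support effective. The documents do not support that: the hypotheses are directional, and half of the two-sided error consists of false findings of harm. A reader might also take 10% as a ceiling for this trial whatever the model. It is one only if each test holds its nominal 5%. Nine centres were randomised (four and five), and the described model names no centre term.

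**Conclusion.** The point holds in a conditional form. The protocol article fixes alpha 0.05 for each of two primary hypotheses under one objective, with two-sided 95% intervals as the criterion and no rule linking them. If either result alone may support a primary claim, and each test holds its nominal level, the two-sided familywise error is 9.75% under independence and at most 10%. The chance of a false claim of benefit is about 4.9%, at most 5%, against 2.5% for one test.

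The conclusion rests on the reading that the staff outcome is also judged at two-sided 5%. It falls away if both outcomes are required. The 84% power figure is the minimum under Holm for each outcome on the stated assumptions; it is not the power that Holm would deliver if both planned effects were present.

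**What to change.** In {20a}, state that the two primary p-values are compared by Holm's procedure: the smaller at 0.025 and, if that succeeds, the other at 0.05. Keep the 95% intervals for estimation. Say explicitly that the rule covers the staff outcome.

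In {14}, state that power at the first Holm step is about 84% for each outcome on the stated assumptions, as a minimum, and about 89% under Holm if both planned effects hold and the tests are independent.

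If the sponsor intends that both outcomes must succeed, write that rule instead. No alpha adjustment is then needed, but {14} should give the joint power (about 81% under independence).

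The cost is a sentence or two and a less favourable power statement. Data collection does not change. No conclusion is lost under Holm when both p-values are below 0.05 and one is below 0.025. Trial status describes data collection as ongoing and no interim analysis is intended, so the rule should be fixed before the primary outcomes are analysed. Holm controls the error only if each p-value is valid with centres as the randomised units, which has to be settled separately.
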